## Abstract

**Background:**

Subacromial impingement syndrome (SIS) is a common clinical condition with a multifactorial etiology. Currently, there is a great variety of therapeutic exercise modalities aimed at treating SIS. Based on alterations of the glenohumeral and/or dysfunctional scapular kinematics associated with SIS, we hypothesize that the implementation of a specific exercise program with special focus on the correction of muscle deficits should be more effective than nonspecific exercises performed at home. This article describes the rationale and methods of study aimed at testing the effectiveness of specific exercise programs versus home exercises in patients with SIS.

**Method/Design:**

Ninety-four patients between the ages of 18 and 50 years referred to the Physical Therapy department of the Clinical Hospital San Borja Arriaran in Chile will be randomized to 2 treatment arms. The intervention group will receive a program of specific exercises with a duration of 12 weeks, taking as a reference the algorithm of clinical decision proposed by a panel of experts. The control group will receive a program of nonspecific exercises to perform at home. Three evaluations will be performed: before the initiation of treatment, and at the 12-week and 1-year follow-up. The primary outcome measure will be the shoulder function by the Constant-Murley questionnaire, and the secondary outcome measures will be the upper extremity function by the Disabilities of the Arm, Shoulder and Hand questionnaire, and pain by the visual analog scale.

**Discussion:**

This article reports the design of a randomized clinical trial aimed at assessing the effectiveness of a specific exercise program versus home exercises in patients with SIS.

**Trial registration:**

Brazilian registry of clinical trials UTN number U1111-1204-0268. Registered 27 September 2017.

## Introduction

1

Subacromial impingement syndrome (SIS), also called external impingement,^[1]^ is defined as a mechanical compression or abrasion of the supraspinatus tendon, subacromial bursa, or long head of the biceps tendon beneath the anterior undersurface of the acromion, coracoacromial ligament, or the acromioclavicular joint during elevation of the arm.^[2]^ It is a very common clinical condition, and represents between 50% and 86% of all consultations for shoulder pain in primary care,^[3–5]^ and 36% in secondary care.^[6]^ Three progressive stages have been defined for this syndrome. In stage 1, a reversible edema and hemorrhage are presented, in patients typically younger than 25 years. In stage 2, chronic inflammation, defined by histological changes such as fibrosis and tendinitis due to repeated mechanical irritation, is usually observed in patients aged 25 to 40 years. Stage 3 typically occurs in individuals older than 40 years with an extended history of shoulder pain with osteophytes or glenohumeral osteoarthrosis, and a partial or full-thickness rotator cuff tear.^[2]^

Currently, SIS is considered a multifactorial condition for which that etiology has been explained by intrinsic and extrinsic mechanisms of rotator cuff pathology.^[7,8]^ The extrinsic factors explain the external mechanical compression of the anatomical structures that are within the subacromial space^[8]^: anatomical factors such as variation in the type and shape of the acromion, the acromioclavicular joint and the thickening of the coracoacromial ligament and biomechanical factors such as alterations in posture, loss of extensibility of the posterior capsule and the pectoralis minor muscle, and alterations in the glenohumeral and scapulohumeral kinematics associated with deficits in the muscular performance of the rotator cuff and the scapular muscles.^[7,8]^

The association between alterations of the glenohumeral and scapular kinematics and SIS has been previously established.^[9–15]^ A meta-analysis found that the pattern of scapular kinematics alterations is characterized by a reduction of the upward and external scapular rotation, and an increase in clavicular elevation and retraction, when compared with healthy asymptomatic subjects.^[11]^ Regarding glenohumeral kinematic changes, a published study showed that patients with SIS only have higher elevation of the humerus in the scapular plane at 30° and 60°, and an increase of the anterior translation of the humeral head between 90° and 120° of anterior flexion, when compared with healthy asymptomatic subjects.^[15]^ These kinematic alterations have been associated with a deficit in the function of some muscles, although there is no consensus on the results of the studies; at the scapulohumeral level, the most significant changes are an increase in the activity of the upper trapezius, a reduction in the activity of the serratus anterior and the inferior trapezius; and a delay in the activation time of the serratus anterior and inferior trapezius.^[9,10,16–19]^ At the glenohumeral level, there is a reduction in the activity and coactivation of the rotator cuff, especially the infraspinatus and subscapular in the first phase of the arm elevation movement.^[7,8,10,16,19]^

Several modalities of exercise have been used for the management of the SIS.^[20–22]^ Previous reviews have shown that therapeutic exercise decrease the pain and improve the function,^[20–26]^ but there is no exercise protocol considered as *“reference standard”* for the conservative treatment of patients with SIS.^[20,21,23,24]^ A consensus decision algorithm for physiotherapists based on clinical reasoning to evaluate and treat patients with shoulder pain have been proposed, in which the selection and prescription of exercises is made based on clinical findings rather than the structural pathology.^[27]^ The specific exercises are the fundamental basis of the treatment, because it seeks to correct muscle deficits and thus restore alterations of the glenohumeral or scapular dysfunctional kinematics associated with SIS.^[22,27]^

This article reports the rationale and methods of a trial aimed to assess the effectiveness in the short- and long term of a program of specific exercises based on the algorithm of clinical decision proposed by a panel of experts, on functional improvement and pain relief compared with exercises at home in patients aged between 18 and 50 years with stage 2 SIS.

## Method

2

### Study design/setting

2.1

This will be a study single-blinded, randomized controlled trial with 2 parallel groups. It will be conducted at the Physical Therapy Department of the Clinical Hospital San Borja Arriaran in Chile. This protocol was written and based on Standard Protocol Items: Recommendations for Interventional Trials guidelines.^[28]^ The participants are residents who will mainly be recruited in the city of Santiago. The participants will be informed about the research, procedures, risks, and benefits by [name] (author of this protocol). If they agree, they will sign an informed consent form. Only those participants who read and agree to the protocol and who sign the informed consent form will be part of the study, following the schedule described in Figure 1.

**Figure 1 F1:**
[figure not shown]
Standard protocol items: Recommendations for Interventional Trials (SPIRIT) figure. BMI = Body mass index, DASH = Disabilities of the Arm, Shoulder and Hand, MMST = Mini-Mental State Test, VAS = visual analog scale.

### Participants

2.2

Ninety-four adult patients with stage 2 SIS based on Neer classification,^[2]^ with a poor response to the initial conservative treatment, and who were under evaluation for surgery, will be included. The diagnosis will be performed by an orthopedic surgeon based on the clinical history according to the following diagnosis criteria: pain located on the anterolateral side of the shoulder for at least 6 months and poor response to initial conservative treatment (at third month). Clinical signs of SIS, such as painful arc during active elevation of the arm, positive Neer or Hawkins-Kennedy test, and pain to the resisted external rotation, to the abduction or positive Empty Can test. These clinical signs have shown sensitivity and specificity values >74% for the diagnosis of SIS.^[29]^ Furthermore, to confirm the exclusion of the other shoulder pathologies, the clinical diagnosis will be complemented with imaging studies,^[30]^ which will include anteroposterior, axial, and outlet radiography, soft tissue echotomography and nuclear magnetic resonance. All patients will be treated with subacromial steroid injection of 40 mg methylprednisolone and 500 mg of oral naproxen twice daily for 14 days; after 2 weeks, they will be referred to the Physical Therapy Department.

#### Inclusion criteria

2.2.1

To participate in the study, the patients will have to fulfill the following inclusion criteria: older than 18 years old, and referred by the Adult Orthopedic Department with a clinical and imaging diagnosis of stage 2 SIS, and with poor response to initial conservative treatment and accept and sign the informed consent.

#### Exclusion criteria

2.2.2

Patients will be excluded if they meet the following criteria: presenting pathologies of cervical origin (cervical radiculopathy, etc), other pathologies of the shoulder joint complex, such as osteoarthritis in the acromioclavicular or glenohumeral joints, calcific tendinitis, adhesive capsulitis, and glenohumeral instability; stage 3 SIS (partial or full-thickness tear rotator cuff); a history of acute trauma, previous surgery, or a previous fracture in the affected shoulder; have previously been infiltrated with corticosteroids in the affected shoulder (6 months); and some degree of cognitive impairment scoring <26 points on the Mini-Mental State Test (MMST).

### Interventions

2.3

The intervention group will receive a specific exercise program based on motor training, taking as a reference the clinical decision algorithm proposed by a panel of experts.^[27]^ In the initial stage, conscious muscular control is necessary to improve proprioception and normalize the rest position scapular,^[22,31]^ for which Mottram et al^[32,33]^ proposed the *“Scapular orientation exercise*.*”* Therefore, 3 scapular control exercises are continued: movement of bilateral anterior flexion of the shoulders up to 60°,^[34,35]^ closed kinetic chain exercise called *“Unilateral bench press*,*”*^[36]^ and scapular control exercise with bilateral shoulder retraction and extension in prone position.^[37]^ Finally, 2 glenohumeral control exercises are prescribed to restore centralization and prevent superior translation of the humeral head: isometric external rotation performed with shoulder adduction^[38]^ and isometric adduction exercise of the shoulder on the scapular plane at 30° and 60°.^[39]^ The exercises should not produce pain; only mild to moderate pain levels (<4/10 on the visual analog scale) are accepted after the session, and a maximum of 4 exercises per session. Dose will be related to the goal of each exercise and will be adjusted in relation to the individual patient, 8 to 10 repetitions of each exercise will be performed, with 5 to 10 seconds of task maintenance and 30 seconds to 1 minute of rest between each repetition. The criteria for exercise progression will be good-quality shoulder movement, and minimal pain increase during exercises. There will be 3 weekly sessions for 12 weeks.

In the control group, all patients will attend an appointment with a physiotherapist, where they will be aware of their clinical condition and will be provided with a printed document with a program of nonspecific exercises to perform at home. This program consists of 6 exercises without external load for the shoulder and cervical spine; movements of shoulder abduction in the frontal plane, shoulder retraction, elevation of the shoulder, retraction of the cervical spine, passive stretching of the upper trapezius, pectoralis major, and minor muscles.^[40,41]^ This will be performed twice a day for 12 weeks. To monitor adherence to treatment, patients will be contacted by phone in the fourth and eighth weeks of treatment.

### Outcome measures

2.4

Baseline and postintervention outcome variables and potential confounders will be measured in both the intervention and control groups. Measurements will be performed before starting the treatment, at the end of twelfth week, and at the 1-year follow-up.

#### Primary outcome measure

2.4.1

Function of the shoulder, as measured by the Constant-Murley questionnaire, will be the primary outcome measure.^[42,43]^ This consists of 4 subscales: 2 based on an interview with the patient regarding pain (a maximum of 15 points will be assigned) and activities of daily living (20 points) and the other 2 based on physical examination about active range of movement (40 points) and muscle strength (25 points), to a maximum score of 100 points.^[42]^ This questionnaire presents a high correlation with other scales and shoulder-specific questionnaires, also showing a high reliability and sensitivity to detect postintervention changes in a wide variety of shoulder pathologies.^[44]^

#### Secondary outcome measures

2.4.2

Upper extremity function, as measured by the Disabilities of the Arm, Shoulder, and Hand questionnaire, is the secondary outcome measure.^[45]^ This is a self-administered questionnaire with 30 items related to the degree of difficulty during the previous week when performing various physical activities due to problems in the shoulder, arm, or hand (21 items); the severity of each of the symptoms, pain related to activity, tingling, weakness, and rigidity (5 items); and the effect of the problem on social activities, work, sleep, and psychological impact (4 items). A rating scale is used that ranges from 1 (without difficulty to perform, without symptoms, or without impact) to 5 (unable to do, very severe, or high impact symptom); the final score ranges from 0 to 100 (the higher the score greater disability). A transcultural adaptation has been made to the Spanish language, whose version showed excellent results with respect to validity, reliability, and sensitivity to change.^[46]^

Pain intensity at rest and movement will be assessed using the visual analog scale, which consists of a horizontal line 10 cm in length, where the left end represents the 0 or *“painless”* and the right end the 10 or *“worst pain imaginable.”* The patient is asked to mark with a vertical line the magnitude of the pain he feels at the time of the evaluation. It is a 1-dimensional, simple, and reproducible assessment method.^[47]^

#### Potential confounders

2.4.3

Clinical variables: dominant shoulder affected, duration of symptoms (months), and previous treatments received in the last 3 months (supervised physical therapy, only exercises, use of paracetamol/nonsteroidal anti-inflammatory drugs, and use of opioids) will be evaluated.

Anthropometry and body composition: weight will be measured with the patient barefoot and in light clothing. Height will be measured using a wall stadiometer, with the patient barefoot and upright and with the sagittal midline touching the back board. Body mass index will be calculated as weight in kilogram divided by the square of the height in meters.

##### Socioeconomic status

2.4.3.1

Educational level will be classified as primary education (functionally illiterate, without any studies, or those not completed primary education), middle education (primary education, high school/secondary education or baccalaureate) and university education (college or PhD degree). Occupation will be categorized as heavy load, light load, and sick leave in the last month.

The cognitive status of all patients will be evaluated using the MMST.^[48]^ This is the most commonly used test for standardized cognitive assessment in the clinical setting.^[49]^ The scores that patients with mild-to-moderate cognitive impairment have for this questionnaire are influenced by a number of sociodemographic variables, such as age and educational level.^[50,51]^ The cut-off scores are, however, variable,^[52]^ we set them at 26/27 in our study to make sure that patients could follow simple commands and could also follow therapeutic indications for their treatments.

### Sample size calculation

2.5

Sample size for this trial is based on an expected mean difference between groups of 17 points of the Constant-Murley questionnaire, which is the minimum clinically important difference.^[53]^ The mean assumed for the calculation was 52.5 with a standard deviation of 23 points based on results of other randomized clinical trials.^[40]^ To detect this difference between both treatments, with a value of α = 0.05 (probability of committing a type I error) and a statistical power of 90%, a minimum of 39 patients per group is needed. This minimal sample size estimate has been increased by 20% after considering the potential dropouts, totaling 47 patients for each group. According to this, the experimental hypothesis proposed is that there will be a difference of at least 17 points in the Constant-Murley questionnaire in the intervention versus control group that will follow a program of exercises at home. Sample size was performed using the Stata SE software, version 15 (StataCorp, College Station, TX).

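### Section 2.5 states a hypothesis of a difference of at least 17 points, but the sample size gives 90% power only against zero difference

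*Protocol article*

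**What the plan says.** Section 2.5 of the protocol article starts from an "expected mean difference between groups of 17 points of the Constant-Murley questionnaire, which is the minimum clinically important difference". It adds: "The mean assumed for the calculation was 52.5 with a standard deviation of 23 points". With α = 0.05 it then gives "a statistical power of 90%, a minimum of 39 patients per group is needed", and this number is "increased by 20% after considering the potential dropouts, totaling 47 patients for each group".

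The next sentence presents the experimental hypothesis as a consequence of that calculation: "there will be a difference of at least 17 points in the Constant-Murley questionnaire in the intervention versus control group".

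Two other places bear on the point. The Abstract (Background) hypothesises only that the specific programme should be more effective than home exercises, with no threshold. Section 2.9 plans a repeated measures analysis of covariance with baseline values as covariates. It mentions no 17-point margin and no null value other than the usual one.

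**The concern.** A planning difference and a hypothesis to be shown are different things. A trial sized to detect 17 points has a high chance of excluding zero if the truth is 17. It does not have a high chance of showing that the truth is 17 or more. Section 2.5 moves from the first to the second as though one followed from the other.

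This matters because the same section calls 17 points the minimum clinically important difference. A hypothesis of at least 17 is thus a claim of clinical relevance, and the quoted power appears to support it. The article also carries two hypotheses of different strength, in the Abstract and in section 2.5, and does not reconcile them. A significant result well below 17 would agree with one and leave the other unshown.

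**Working it through.** **Inputs (section 2.5).** Difference 17, SD 23, α = 0.05, power 90%, equal groups, 39 per group before and 47 after the dropout allowance. Sidedness is not stated.

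**Step 1: reproduce the stated figure.** For a two-sided test of zero difference with true difference 17:

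n = 2 × (1.960 + 1.282)² × 23² / 17² = 38.5, rounded up to 39 per group.

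This matches. One-sided α = 0.05 gives 32 and does not match. An exact t-test calculation gives 40, with 89.7% power at 39. The allowance also matches: 39 × 1.2 = 46.8, rounded up to 47.

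**Step 2: could the null be 17?** The formula would then divide by (true difference − 17)². With an expected difference of 17 the divisor is zero, so no sample size gives 90% power. The 39 can only refer to a null of zero.

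**Step 3: what reaches significance against zero** (unadjusted two-group comparison, SD 23).

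| | 39 per group | 47 per group |
|---|---|---|
| SE = 23 × √(2/n) | 5.21 | 4.74 |
| Smallest significant observed difference (t critical value × SE) | 10.4 | 9.4 |
| 95% CI if the observed difference is 17 | 6.6 to 27.4 | 7.6 to 26.4 |
| Observed difference at which the lower limit passes 17 | 27.4 | 26.4 |

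**Step 4: behaviour when the true difference is exactly 17.** The lower 95% limit exceeds 17 with probability 2.5%. This follows from the definition of the interval, so it does not depend on n, SD or adjustment. With 39 per group, power against zero is 0.897. Half of all estimates fall below 17, so about 0.897 − 0.5 = 0.397 of trials, or 40%, are significant with an estimate below 17.

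**Step 5: behaviour when the hypothesis in section 2.5 is false.** Take a true difference of 12 (an assumed value; the article gives none). The test against zero is significant with probability about 62% (39 per group) or 71% (47 per group).

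**Step 6: what 90% power for more than 17 would take.** With 39 per group, the true difference would have to be about 17 + 3.24 × 5.21 = 33.9. With 47 per group it would be about 17 + 3.24 × 4.74 = 32.4. For other assumed true differences, the numbers per group before dropout are 1236 (true 20), 174 (true 25) and 66 (true 30).

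**The case against.** The strongest reply is that the sentence merely restates the planning alternative. It follows directly on the arithmetic and repeats the same 17 points, and an experimental hypothesis can be read as what the investigators expect to find. The ordinary superiority hypothesis is already in the Abstract, and the aims elsewhere carry no threshold. The article never writes out a null hypothesis, so the zero null is an inference. This is largely fair, and it is why the point is minor. It does not remove the mismatch: the sentence is the article's formal statement of its experimental hypothesis, and it puts a number on that hypothesis which the quoted power does not cover.

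Three stronger readings are tempting and are not supported:

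- *That the trial is too small.* It is not. The 39 is correct for the usual superiority test by the normal formula. A larger trial would be needed only if at least 17 were truly meant as the hypothesis to be shown.
- *That the investigators plan to report any significant result as confirming 17 points or more.* Nothing in the article says so. A rule for reading the interval against 17 may also properly sit in a full protocol or analysis plan that is not shown.
- *That a significant estimate somewhat below 17, say 14, would refute the hypothesis.* With 39 per group its interval is 14 ± 10.4, about 3.6 to 24.4. That includes 17, so it would neither establish nor refute a difference of at least 17.

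It is also fair that the figures describe an unadjusted comparison, whereas section 2.9 adjusts for baseline and imputes missing values. Adjustment would reduce the SE and so move the significance threshold further below 17. It would also lower the true difference needed in Step 6. The mismatch remains in either case.

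**Conclusion.** The point holds as a minor correction. Section 2.5 derives a hypothesis of at least 17 points from a calculation that gives 90% power only to reject zero when the truth is 17. No planned test addresses 17, and the Abstract states plain superiority.

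In size, significance begins about 6.6 points below the hypothesised minimum with 39 per group (17 − 10.4) and about 7.6 below with 47 (17 − 9.4). Under the planning assumption itself, the interval would lie wholly above 17 in only 2.5% of trials.

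The thresholds rest on SD 23, an unadjusted comparison, and 39 or 47 analysed per group. The 2.5% rests on none of these. The zero null is inferred from the exact match to 39 and from the absence of any margin in section 2.9.

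**What to change.** In section 2.5, replace the hypothesis sentence with a superiority statement consistent with the Abstract: a non-zero mean difference in Constant-Murley score in favour of the specific programme, tested two-sided. Keep 17 points, described as the difference used for planning. Add that the estimate and its 95% confidence interval will be reported against 17 points, so that a significant result alone is not presented as showing a benefit of at least 17.

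The cost is a sentence or two of text. Sample size, analysis and conduct stay as they are. The only thing given up is the suggestion that the trial is powered to show a benefit of 17 points or more.
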